#### Subgroup analysis

For primary outcomes, we will conduct a subgroup analysis using initial EPDS, socio-economic factors, adverse childhood experiences, and social support.

#### Sensitivity analysis

We will use a complete analysis based upon the assumption missing completely at random. We will conduct a sensitivity analysis using an inverse probability weighted generalized estimating equation to estimate the dropout mechanism. As previous study has indicated that socio-economic status such as education and household income influenced the attrition rate [30] and we supposed that initial depressive symptoms would possibly influence adherence to the program, this study will use baseline scores of the EPDS, and socio-economic status (highest education, income) as weighting factors.

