Internet-based psychotherapy not only reduces practical barriers to access for users but may also reduce psychological barriers. Previous evidence has shown that many women with postnatal depression struggle with stigmatization, and this can be an obstacle for health care providers attempting to connect depressed mothers with medical care [43, 44]. In qualitative studies of iBA for postnatal depression, mothers who reported struggling with stigma stated that they found internet intervention more acceptable than face-to-face intervention [45]. We expect that internet-based interventions including smartphones, which have become such standard communication tools, would make it easier for mothers in need to seek care for their mental health. Internet-based psychotherapy, however, has its own challenges. Many studies have described the high attrition rate of internet-based psychotherapy, ranging from 9.7 to 78.9% of the participants, as a weakness of web-based interventions [40, 46]. Internet-based interventions demonstrated improved retention rates with human support [28, 32, 41, 47–49]; however, the adequate intensity of support needed to achieve the goal is still unknown. As the implementation of the program involves not only the users but also medical providers and hospital managers, it is essential to understand how the program is perceived in terms of acceptability, appropriateness, feasibility, and potential harm perceived by these stakeholders.

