### Statistical methods

#### Clinical efficacy

For primary outcomes, an analysis of covariance (ANCOVA) will be conducted to compare the mean differences of co-primary outcomes at 24 weeks follow-up between the intervention and TAU groups after adjusting baseline scores. The study sets two co-primary outcomes, including the EPDS scores at 24 weeks after the initiation of the program and psychological aggression toward children measured by the CTS-1 scores at the 24 weeks follow-up survey. The order of statistical testing is as follows: (1) the EPDS scores at 24 weeks follow-up; (2) CTS-1 scores at 24 weeks follow-up. If we find statistical significance for the EPDS scores at the predefined 0.05 level, then we will conduct statistical testing for the CTS-1 scores. If we do not find statistical significance for the EPDS scores, we will conduct the ANCOVA for the CTS-1 score as a complementary analysis. Given the fixed-sequence testing procedure, the study will not adjust for the multiplicity of each statistical test.

For secondary outcomes, the ANCOVA will be conducted to compare secondary outcome measures (Table 2) between the TAU and intervention groups after adjusting baseline scores. Statistical analyses will be performed using the SAS version 9.4 (SAS Institute, Cary, North Carolina, USA).

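### Complete-case ANCOVA under MCAR conflicts with the plan's own statement on attrition, and the weighted sensitivity analysis as listed cannot reveal bias from dropout tied to arm together with on-study symptoms or SES

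*Protocol article*

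**What the plan says.** Under Clinical efficacy, the protocol article states that "an analysis of covariance (ANCOVA) will be conducted to compare the mean differences of co-primary outcomes at 24 weeks follow-up", adjusted for baseline scores. Under Sensitivity analysis it fixes the handling of missing data: "We will use a complete analysis based upon the assumption missing completely at random". It then adds: "We will conduct a sensitivity analysis using an inverse probability weighted generalized estimating equation to estimate the dropout mechanism".

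The reason given for the weights is that "previous study has indicated that socio-economic status such as education and household income influenced the attrition rate", and that "we supposed that initial depressive symptoms would possibly influence adherence to the program". The factors follow: "this study will use baseline scores of the EPDS, and socio-economic status (highest education, income) as weighting factors".

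Three other places bear on the point:

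- Outcomes and Table 2 schedule EPDS and CTS-1 at baseline, 12 weeks and 24 weeks in both arms.
- Intervention program gives the iBA arm alone 12 weekly sessions of 30 minutes, and Study design says the trial is non-blinded.
- Background cites a "high attrition rate of internet-based psychotherapy, ranging from 9.7 to 78.9% of the participants".

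**The concern.** Dropout that depends on education and income is not missing completely at random, so the assumption behind the primary analysis is at odds with the evidence cited to justify the sensitivity analysis. The primary model does not contain those variables either. It also leaves out any mother who answered at 12 weeks but not at 24, although her 12-week score says something about her likely 24-week score.

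The weights would be expected to repair this. As listed, they treat two mothers with the same baseline EPDS, education and income alike, whichever arm they are in and however they were doing at 12 weeks. If mothers leave the iBA arm for reasons linked to how they are doing, and TAU mothers do not, the weights cannot see it. At stake is a sensitivity analysis that agrees with a biased primary result and is read as support for it. Because CTS-1 is tested after EPDS in a fixed sequence at 0.05, a false positive on EPDS would also open the confirmatory CTS-1 test.

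**Working it through.** **Inputs from the article.** Allocation 1:1; planned follow-up 85% (EPDS) and 80% (CTS-1); planned effects d = 0.55 (EPDS, high EPDS group), 0.50 and 0.40 (CTS-1, high and low EPDS groups); 75 per arm in the high EPDS group. Dropout by arm is not given.

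**The plan's own figure.** A two-sided t-test with d = 0.55 and 80% power needs 53 per arm; 53 / 0.85 = 62.4, so 63 per arm and 126 in total, against the stated 128. This agrees within two participants and shows that the 0.05 level is two-sided. The missing-data point itself rests on no stated figure.

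**Check by simulation (assumptions, not document figures).** One million subjects, no true effect, 80% followed up overall. The 24-week score is 0.15 × baseline − 0.15 × SES + 0.6 × 12-week score + noise (SD 0.65), rescaled to SD 1 in the control arm. Three estimators were compared: completer ANCOVA with baseline; the same model weighted from a dropout model with baseline EPDS and SES, as the article lists; and the same model with weights from arm, baseline, SES, 12-week score and their arm interactions. Bias is in SD; negative favours iBA.

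| Dropout depends on | Follow-up iBA / TAU | Completer ANCOVA | Listed weights | Weights with arm and 12-week score |
|---|---|---|---|---|
| arm alone | 73% / 87% | 0.00 | 0.00 | 0.00 |
| arm × baseline EPDS | 75% / 85% | 0.00 | 0.00 | 0.00 |
| 12-week score, same in both arms | 80% / 80% | 0.00 | 0.00 | 0.00 |
| arm × SES | 75% / 85% | −0.04 | −0.05 | 0.00 |
| arm × 12-week score, odds ratio 2 | 75% / 85% | −0.07 | −0.07 | 0.00 |
| arm × 12-week score, odds ratio 3 | 74% / 86% | −0.11 | −0.11 | 0.00 |
| 12-week score, opposite direction by arm | 80% / 80% | −0.11 | −0.11 | 0.00 |

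The odds ratios are per unit of 12-week score, about 1 SD, in the iBA arm. In the last four rows the two planned analyses agree with each other and are both wrong.

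**Direction.** In a separate run with 25% iBA and 15% TAU dropout and log-odds 0.5 to 1.0, the completer bias was 0.045 to 0.083 SD towards iBA when mothers doing badly left. It was 0.048 to 0.081 SD against iBA when improved mothers left, and 0.014 to 0.033 SD when TAU had the same slope.

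**Size against the plan.** 0.04 / 0.55 = 7% and 0.11 / 0.55 = 20% of the planned EPDS effect. With 75 × 0.80 = 60 completers per arm, SE = √(2/60) = 0.183. A bias of 0.04 shifts the test statistic by 0.04 / 0.183 = 0.22, and one of 0.11 by 0.60. From P(Z > 1.96 − shift) + P(Z < −1.96 − shift), the two-sided error is about 5.6% and 9%. Baseline adjustment would reduce the SE and so raise these slightly.

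**CTS-1.** If dropout is driven by depression and EPDS and CTS-1 correlate at an assumed 0.3, the CTS-1 bias is 0.01 to 0.04 SD. With 195 × 0.80 = 156 completers per arm, the error is about 5 to 6%.

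**The case against.** A simple primary analysis with a pre-specified sensitivity analysis under a weaker assumption is a common design, and the article does act on the SES evidence: that is why the weights exist. The article may also condense the weight model; arm terms and visit-wise weights could sit in an analysis plan that is not shown, and a GEE may use the 12-week scores as repeated outcomes. Background notes that human support improves retention; this programme has therapist feedback, and weekly reminders go to anyone who has not completed a follow-up survey. Any replacement relies on MAR, which cannot be verified, and gains little for women who miss both surveys.

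Most of this limits the size of the point. It does not remove it: the MCAR assumption and the weighting factors are affirmative statements, and 12-week scores used as GEE outcomes would not by that alone enter the weights.

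Several stronger readings are tempting and are not supported:

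- *Any difference in dropout between arms biases the result.* It does not; the mechanism must combine arm with SES or on-study symptoms.
- *The plan contradicts MCAR twice.* Only the SES statement concerns attrition. The depression statement concerns adherence to the programme, which is not survey non-response.
- *The bias favours iBA.* The documents give no direction, and it reverses if improved mothers leave.
- *The bias could reach 0.16 SD, 29% of d = 0.55.* That takes stronger assumptions, with iBA dropout of up to 40%, against a planned loss of 15 to 20%.
- *CTS-1 error rises to about 11%.* That takes a 0.08 SD bias in CTS-1 itself, so dropout would have to be driven by CTS-1 and not by depression.

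**Conclusion.** The point holds in a limited form. The MCAR assumption is inconsistent with the SES evidence in the same paragraph. The listed weights omit arm and the 12-week scores, so where dropout depends on arm jointly with SES or on-study symptoms, the planned sensitivity analysis carries about the same bias as the primary one. Near the planned 80% follow-up that bias is about 0.04 to 0.11 SD for an outcome whose own 12-week score drives dropout, and 0.04 to 0.05 SD in the SES case examined. It can go either way and is likely smaller for CTS-1 if depression is the driver.

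These sizes rest on assumed dropout slopes, since the article gives no dropout by arm. For dropout that depends only on arm and the baseline score, the ANCOVA is sound if the model is linear, so it needs less than its MCAR label suggests. The textual inconsistency is certain; the practical impact is moderate and uncertain. It is worth settling before the data are analysed.

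**What to change.** Make the primary analysis a likelihood-based repeated-measures model on the 12- and 24-week scores of all randomised mothers in each outcome's analysis population, or multiple imputation by arm that uses the 12-week scores. Include the baseline score, the stratification factors, education and income, and take the treatment contrast at 24 weeks. Keep completer ANCOVA as a sensitivity analysis, and replace the MCAR statement with the assumption actually relied on.

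If the weighted GEE is kept, use visit-wise (stepwise) weights with arm, the 12-week scores and arm interactions. The stepwise form is needed because women who miss both surveys have no 12-week score.

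The cost is a change of wording and some extra SAS programming; the outcome and weighting variables are already planned. The analysis would then rely on MAR, which is still unverifiable but weaker than the MCAR now assumed.

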#### Data confidentiality

Information on individuals acquired through this study will be anonymized. The correspondence table of program ID and individual information will be created and stored in the Department of Mental Health, Graduate School, University of Tokyo. The research data collected in online surveys will be temporarily stored in the Amazon Elastic Compute Cloud system (Amazon Web Services, Inc.). The data will be moved to a password-locked PC in the Department of Mental Health, Graduate School, University of Tokyo. Only principal investigators will have access to the final data sets.

#### Data monitoring

This study does not have an external data monitoring board; however, we will have regular meetings to discuss our current status of recruitment and data collection with external medical providers and researchers.

## Discussion

The strength of the study is that it evaluates the effectiveness of the iBA program for maternal depressive symptoms and psychological aggression toward children in a randomized-controlled trial. The study also intends to examine the implementation outcomes of the iBA program, which is essential in delivering the program to the population in need. The limitation of the study is that all the outcomes are measured by the self-report scales. Although all the postnatal mothers are recruited in the postnatal check-up at one month after delivery, the time that they complete the baseline online survey and finish enrolment may differ. This may influence the baseline EPDS scores. Moreover, the participants are to be recruited in relatively large hospitals, and the finding of the study may not be generalizable to the postnatal women having deliveries at smaller hospitals and clinics.

The results of the study may be relevant and beneficial to the health care needs of postnatal women and their children, as well as in providing future directions to health policy for postnatal care and child abuse prevention.

## Data Availability

The manuscript consists of a trial protocol. Data sharing is not applicable; no datasets were generated or analysed in the preparation of this protocol.

## Abbreviations

BA: behavioural activation
CBT: cognitive behavioural therapy
iBA: internet-based behavioural activation
iCBT: internet-based cognitive behavioural therapy
EPDS: Edinburgh Postnatal Depression Scale
TAU: treatment as usual
QOL: quality of life
TRAPs: Triggers-Reactions-Avoidance Patterns
CTS-1: Conflict Tactics Scale 1
PHQ-9: Patient Health Questionnaire-9
PSI-SF: Parental stress index-short form
MIBS-J: Mother-to-Infant Bonding Scale Japanese version
EQ-5D-5L: EuroQol-5 dimension-5 level
DPT-IPV: diphtheria, tetanus, pertussis, and polio
iOSDMH: Implementation outcome scale for Digital Mental Health
SUS: System Usability Scale
ANOVA: analysis of covariance
